##### Patient Demographics and Treatment Variables

2.12.2.1

A structured data abstraction form and interviewer‐administered questionnaire will be used to collect participants' socio‐demographic, clinical, behavioral, and treatment‐related information under the supervision of the research team, which includes the principal investigator, a statistician, a clinical pharmacist, and senior medical experts. Trained research nurses will collect the data, while the principal investigator will oversee data quality through regular monitoring and validation.

Variables to be collected include age, sex, duration since HIV diagnosis, duration on ART, baseline and follow‐up HIV viral load, CD4 count, HBV serological status, comorbidities, concurrent medications, medication adherence, Health Belief Model (HBM) constructs, retention in care, and HIV–HBV‐related knowledge scores. These variables will be recorded at baseline and reassessed at the 6‐month follow‐up to evaluate changes over time and estimate the effect of the intervention.

Data will be obtained from participant interviews, patient medical records, laboratory reports, pharmacy refill records, and health facility electronic databases where available. All collected data will be anonymized by assigning unique study identification numbers before analysis to ensure participant confidentiality. Electronic datasets will be securely stored on password‐protected computers accessible only to authorized members of the research team.

Ethical approval will be obtained from the Institutional Review Board of the University of Gondar. Written informed consent will be obtained from all participants before enrollment. Permission to use standardized questionnaires and assessment tools will be secured from the respective developers or authorized sources prior to data collection.

#### The Health Belief Model Questionnaires

2.12.3

Data on participants' knowledge regarding HIV–HBV co‐infection and Health Belief Model (HBM) constructs will be collected at baseline (enrollment) and at the end of the 6‐month follow‐up period using a structured interviewer‐administered questionnaire. The questionnaire will assess knowledge (15 items) and the six core HBM domains, including perceived susceptibility (8 items), perceived severity (7 items), perceived benefits (8 items), perceived barriers (7 items), self‐efficacy (8 items), and cues to action (6 items).

Responses to HBM items will be measured using a 5‐point Likert scale ranging from 1 (strongly disagree) to 5 (strongly agree), reflecting participants' perceptions, beliefs, motivation, and confidence regarding adherence to recommended HIV–HBV‐related health behaviors, including medication adherence, clinic attendance, and self‐management practices. Knowledge items will be scored based on correct responses, and a composite knowledge score will be generated, with higher scores indicating better knowledge. Composite scores will also be calculated for each HBM construct by summing item responses, with higher scores indicating stronger beliefs within the respective domains. Changes in knowledge and HBM construct scores between baseline and the 6‐month follow‐up assessment will be evaluated to determine the effect of the patient‐centered education intervention [27].

#### Virological Suppression

2.12.4

HIV viral load measured at baseline and at the end of the 6‐month follow‐up period will be used to assess virological outcomes. The primary virological outcome will be evaluated as the change in log‐transformed HIV viral load (log_10_ copies/mL) between baseline and follow‐up. In addition, virological suppression will be assessed as a secondary clinical outcome and will be defined as an HIV viral load of < 1000 copies/mL at the 6‐month follow‐up assessment, consistent with recommended clinical thresholds for treatment success. HIV RNA levels will be measured using a real‐time polymerase chain reaction (PCR) assay. Blood samples or routine laboratory viral load testing reports will be obtained through referral hospital laboratories accredited for HIV viral load testing. Additional clinical information related to virological outcomes will also be extracted from participants' medical records and laboratory reports.

#### Medication Adherence

2.12.5

Medication adherence will be assessed at baseline and at the end of the 6‐month follow‐up period using a context‐adapted version of the Hill‐Bone Medication Adherence Scale (HBMAS), a widely used, simple, and reliable self‐report instrument for evaluating adherence behaviors in chronic disease management. For this study, the scale has been adapted to assess adherence to ART and HBV‐active medications among adults living with HIV‐HBV co‐infection.

The adapted HBMAS evaluates three key adherence domains: medication‐taking behavior, appointment keeping, and prescription refilling, while maintaining the original conceptual framework of the instrument. Responses will be recorded using a Likert‐type scale, and item scores will be summed to generate a total adherence score, with higher total scores indicating poorer medication adherence.

Medication adherence will primarily be analyzed as a continuous outcome using the total HBMAS score to assess changes in adherence between baseline and the 6‐month follow‐up period. Mean changes in adherence scores between the intervention and comparison groups will be evaluated to estimate the effect of the patient‐centered education intervention. Additionally, adherence will be categorized as good or poor based on predefined cut‐off values derived from the total HBMAS score for supplementary categorical analyzes. Associations between the intervention and adherence status at follow‐up will be explored using appropriate regression models while adjusting for relevant baseline covariates. The adapted HBMAS has been widely used in clinical and research settings and is considered an appropriate tool for identifying varying levels of medication adherence in this study population [23, 24].

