##### Medication Adherence

2.10.2.1

Medication adherence will be assessed at baseline and at the scheduled 6‐month follow‐up visit in both the intervention and comparison groups using a context‐adapted version of the Hill‐Bone Medication Adherence Scale (HBMAS) [23]. Medication adherence will be evaluated over the same 6‐month post‐enrollment follow‐up period used for assessment of the primary outcome, ensuring a comparable observation window across study arms.

The HBMAS is a validated self‐report instrument designed to assess adherence behaviors among individuals receiving long‐term therapy and has been adapted to capture adherence to ART and HBV‐active medications among adults living with HIV or HIV–HBV co‐infection [23, 24]. The adapted HBMAS assesses three domains of adherence: medication‐taking behavior, appointment keeping, and prescription refilling. Responses are recorded using a Likert‐type scale, and item scores are summed to generate a total adherence score, with higher scores indicating poorer adherence.

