##### Retention in Care

2.10.2.3

Retention in care will be assessed over the same 6‐month follow‐up period in both groups and measured based on participants' attendance at scheduled clinic visits and continuity of follow‐up care. This outcome will be used to evaluate ongoing engagement with HIV‐HBV care services.

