#### Exploratory Outcomes

2.10.3

Exploratory analyzes will be conducted to identify sociodemographic, clinical, and behavioral factors associated with virological response. In addition, the relationships among changes in HIV–HBV‐related knowledge, medication adherence, retention in care, and virological outcomes will be examined using correlation and multivariable regression analyzes. All exploratory variables will be collected during the same follow‐up period and assessed at equivalent time points across both study groups.

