#### Medication Adherence

2.13.2

a secondary outcome variable, will be measured using a context‐adapted version of the Hill‐Bone Medication Adherence Scale (HBMAS). The HBMAS is a validated self‐report instrument originally developed to assess medication‐taking behaviors in chronic disease management and has been widely used in both clinical practice and research settings. For the present study, the scale has been adapted to assess adherence to ART and HBV‐active medications among adults living with HIV–HBV co‐infection. Item wording has been modified to reflect ART dosing schedules, routine HIV clinic attendance, and prescription refilling practices while preserving the original conceptual domains of medication‐taking behavior, appointment keeping, and prescription refilling.

Responses to the adapted HBMAS will be recorded using a Likert‐type response scale, with higher scores indicating poorer medication adherence. A composite adherence score will be calculated by summing individual item responses. Medication adherence will primarily be analyzed as a continuous outcome using the total adherence score to evaluate changes between baseline and the 6‐month follow‐up period. For supplementary analyzes, adherence will also be categorized into predefined adherence levels (e.g., good vs. poor adherence), with lower scores representing better adherence and higher scores indicating suboptimal adherence.

The adapted scale will undergo translation and back‐translation procedures to ensure linguistic and conceptual equivalence. Internal consistency reliability will be assessed using Cronbach's alpha prior to analysis. The context‐adapted HBMAS is considered an appropriate and reliable tool for assessing medication adherence among adults living with HIV in the study setting [23, 24].

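### The adherence total includes appointment-keeping items while retention is defined by visit attendance, so the two secondary outcomes overlap and their planned association is partly built in

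*Protocol article*

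**What the plan says.** All references are to the protocol article.

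- **Adherence objective (2.1.2).** The aim is adherence to ART and HBV-active medications, measured with the adapted Hill-Bone scale (HBMAS).
- **Content of the scale (2.10.2.1, 2.12.5, 2.13.2).** It covers "three key adherence domains: medication‐taking behavior, appointment keeping, and prescription refilling". Section 2.13.2 says the items were reworded to reflect, among other things, "routine HIV clinic attendance, and prescription refilling practices while preserving the original conceptual domains".
- **Scoring and analysed variable (2.12.5).** "item scores will be summed to generate a total adherence score, with higher total scores indicating poorer medication adherence". Further, "Medication adherence will primarily be analyzed as a continuous outcome using the total HBMAS score". The good/poor split is cut from the same total. No domain score is mentioned.
- **Retention (2.1.2, 2.10.2.3).** This is a separate secondary outcome, measured by "attendance at scheduled clinic visits" and continuity of follow-up over the same 6 months. Section 2.1.2 adds routine clinical monitoring.
- **Analysis that joins them (2.10.3).** Relationships among changes in knowledge, "medication adherence, retention in care, and virological outcomes will be examined using correlation and multivariable regression analyzes". This is labelled exploratory.
- **Data sources.** The HBMAS is a "validated self‐report instrument designed to assess adherence behaviors" (2.10.2.1). Section 2.12.2 takes clinic attendance, retention and refill history from medical records. Section 2.11.3 lists baseline retention among the questionnaire content for the intervention group.

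The article does not mention the overlap between the two measures.

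**The concern.** A participant whose pill-taking is unchanged but who keeps appointments better will tend to score better on the adherence total and also on retention. Two things follow.

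First, the adherence–retention association in 2.10.3 would be expected to differ from zero even if taking the drugs and attending the clinic were unrelated, because the total contains attendance items. A higher HBMAS total means poorer adherence, so the artefact is a negative correlation. It would be read as better adherence going with better retention.

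Second, the between-group comparisons of the two secondary outcomes are not separate evidence. In this trial the programme may itself act on attendance. Sessions are monthly and take place at ART visits (2.9.1, 2.11.3). Intervention participants who miss a session are contacted and rebooked where feasible (2.11.3), and no equivalent is described for the comparison hospital. Appointment items could therefore improve in one arm through delivery of the programme. That single change could appear once as better medication adherence and again as better retention.

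**Working it through.** There is no figure in the plan to reproduce on this point. The definitions establish the overlap, and arithmetic can only show how large it might be.

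**Step 1: definitions side by side**

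| Content | In the HBMAS total? | In the retention definition? |
|---|---|---|
| Medication-taking | yes | no |
| Appointment keeping | yes | yes (visit attendance) |
| Prescription refilling | yes | no |

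Only the appointment row appears in both.

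**Step 2: size of the built-in correlation**

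Assumptions, none of them given in the article:
- a, b and c items on pill-taking, appointments and refills, with equal item variances;
- inter-item correlation ρ within a domain, and domains independent of each other;
- pill-taking and refilling unrelated to retention;
- r, the correlation of the self-reported appointment sub-score with retention. It is below 1 because one is self-report and the other comes mainly from records.

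The variance of an m-item sub-score is V(m) = m + m(m−1)ρ. Then

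|corr(total, retention)| = r × √[V(b) / (V(a) + V(b) + V(c))].

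Worked example, split 6/2/2 and ρ = 0.2: V(6) = 6 + 30 × 0.2 = 12 and V(2) = 2 + 2 × 0.2 = 2.4. The ratio is 2.4/16.8 = 0.143, with square root 0.378. With r = 0.3 this gives 0.11, and with r = 0.7 it gives 0.26.

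| Split a/b/c | ρ | r = 0.3 | r = 0.7 |
|---|---|---|---|
| 8/1/1 | 0.5 | 0.05 | 0.11 |
| 8/1/1 | 0.2 | 0.07 | 0.15 |
| 9/2/3 | 0.5 | 0.07 | 0.16 |
| 9/2/3 | 0.2 | 0.08 | 0.20 |
| 6/2/2 | 0.5 | 0.10 | 0.23 |
| 6/2/2 | 0.2 | 0.11 | 0.26 |
| 4/3/3 | 0.5 | 0.16 | 0.37 |
| 4/3/3 | 0.2 | 0.16 | 0.37 |

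The range is about 0.05 to 0.37. Only a perfect sub-score–retention correlation (r = 1) would take it to 0.16 to 0.53 over the same splits.

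**Step 3: chance of p < 0.05 from overlap alone**

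Section 2.7 expects 20% loss, so 120 × 0.80 = 96 with endline data. By Fisher's z, the chance is Φ(atanh(|corr|) × √93 − 1.96). Over the table it runs from about 7% (8/1/1, ρ = 0.5, r = 0.3) to about 97% (4/3/3, ρ = 0.2, r = 0.7). For the 6/2/2 split it is about 16% to 74%. A range this wide shows the effect cannot be pinned down from the article.

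**Step 4: why the refill items matter to the size**

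Take 12 items, 10 on pill-taking, 1 on appointments and 1 on refills, with ρ = 0.5 and an item–attendance correlation of 0.707. V(10) = 10 + 90 × 0.5 = 55.
- Only the appointment item tracks attendance: 0.707/√(55 + 1 + 1) = 0.09.
- The refill item is also treated as an attendance item: V(2) = 2 + 2 × 0.5 = 3, and 1.414/√(55 + 3) = 0.19.

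Counting refills as attendance doubles the figure here, and the stated retention definition does not justify it.

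**Step 5: after the change**

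With the appointment items left out of the adherence score, the overlap-induced correlation is 0 under the same assumptions.

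**The case against.** The strongest points on the other side are these.

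- **Summing the domains follows the instrument.** Section 2.12.5 describes the scale as covering "appointment keeping, and prescription refilling, while maintaining the original conceptual framework of the instrument", and 2.1.2 names the HBMAS as the adherence measure. This stands: the total is a legitimate score, and the difficulty arises only when it is set beside an attendance-based outcome.
- **The two measures are not the same data.** A reader might infer that one record of attendance is counted twice. The article does not support that: the HBMAS is self-reported, and section 2.12.2 takes attendance and retention from records. The questionnaire mention in 2.11.3 concerns baseline only. What is shared is the construct.
- **Refills.** A reader might count refill items as overlapping too. The retention definitions do not include refilling, and 2.12.2 lists refill history separately.
- **Regression.** A reader might infer that adherence and retention enter one viral-load model and distort each other's coefficients. Section 2.10.3 does not say so. The covariate list in 2.15 contains neither, the abstract's list contains adherence but not retention, and 2.15 checks multicollinearity.
- **Completers.** Participants lost to follow-up have no endline HBMAS. If the worst retained leave, the spread of retention narrows among those analysed and the artefact shrinks. This stands and is not in the calculation.
- **Left to another document.** Domain scores are often specified in the full protocol or analysis plan, which are not shown. That carries some weight, but the article itself fixes the total as the analysed variable and plans the analysis that joins it to retention.

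The 2.10.3 analysis is also exploratory, and sections 2.15 and 4 call for cautious interpretation of a pilot. That limits the impact without removing the overlap.

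**Conclusion.** The point holds in limited form. Appointment-keeping content is in the adherence total, and visit attendance defines retention over the same 6 months. The exploratory association between them is therefore partly built in, and an effect on attendance alone could move both secondary outcomes. The primary viral-load outcome is untouched.

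The size is not determinable from the article. For item splits from 8/1/1 to 4/3/3, inter-item correlation 0.2 to 0.5 and a sub-score–retention correlation of 0.3 to 0.7, overlap alone gives an absolute correlation of about 0.05 to 0.37. A reader might infer that a significant association is close to guaranteed. That would require most of the scale to be about attendance, or self-report to track the records very closely, and the article establishes neither. Nor does the overlap justify refusing any adherence claim unless the medication-taking domain moves, since that would place a debatable gate on the instrument's own total. This is a worthwhile, inexpensive improvement and not a flaw in the main result.

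**What to change.** 1. In 2.12.5 and 2.13.2, state that the medication-taking domain score will be derived in addition to the total.
2. In 2.10.3, for analyses that involve retention, use an adherence score without the appointment-keeping items.
3. For the secondary adherence outcome, keep the total as stated and report the between-group change in the medication-taking score beside it.
4. State that adherence and retention share attendance content and are not to be read as independent benefits.

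The cost is analysis wording and one extra line in the results, since the items are already collected. The downside is that the medication-taking score has fewer items and will be somewhat less reliable than the total. Fixing this before analysis also avoids choosing a domain after the results are known.

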### Variable Measurement and Definition

2.13

#### Virological Suppression (HIV)

2.13.1

Virological suppression will be defined as an HIV viral load of < 1000 copies/mL of plasma, or below the laboratory assay detection limit where applicable, based on the most recent viral load measurement. This definition is consistent with the World Health Organization (WHO) criteria for monitoring ART response and treatment success [28].

#### Medication Adherence

2.13.2

a secondary outcome variable, will be measured using a context‐adapted version of the Hill‐Bone Medication Adherence Scale (HBMAS). The HBMAS is a validated self‐report instrument originally developed to assess medication‐taking behaviors in chronic disease management and has been widely used in both clinical practice and research settings. For the present study, the scale has been adapted to assess adherence to ART and HBV‐active medications among adults living with HIV–HBV co‐infection. Item wording has been modified to reflect ART dosing schedules, routine HIV clinic attendance, and prescription refilling practices while preserving the original conceptual domains of medication‐taking behavior, appointment keeping, and prescription refilling.

Responses to the adapted HBMAS will be recorded using a Likert‐type response scale, with higher scores indicating poorer medication adherence. A composite adherence score will be calculated by summing individual item responses. Medication adherence will primarily be analyzed as a continuous outcome using the total adherence score to evaluate changes between baseline and the 6‐month follow‐up period. For supplementary analyzes, adherence will also be categorized into predefined adherence levels (e.g., good vs. poor adherence), with lower scores representing better adherence and higher scores indicating suboptimal adherence.

The adapted scale will undergo translation and back‐translation procedures to ensure linguistic and conceptual equivalence. Internal consistency reliability will be assessed using Cronbach's alpha prior to analysis. The context‐adapted HBMAS is considered an appropriate and reliable tool for assessing medication adherence among adults living with HIV in the study setting [23, 24].

### Qualitative Data

2.14

A qualitative study will be conducted at the end of the intervention period to explore the acceptability, feasibility, and perceived usefulness of the patient‐centered health education intervention among adults living with HIV receiving ART, healthcare providers, and hospital leaders in North‐West Ethiopia. A sequential interpretive descriptive qualitative approach will be employed to obtain an in‐depth understanding of participants' experiences, perceptions, and contextual factors influencing the implementation of the intervention.

Data will be collected using three qualitative methods: focus group discussions (FGDs) with adults living with HIV–HBV co‐infection, in‐depth interviews (IDIs) with healthcare providers involved in HIV/HBV care, and key informant interviews (KIIs) with hospital leaders and program managers. These methods will enable exploration of patient experiences, provider perspectives, and institutional‐level barriers and facilitators related to implementation and sustainability of the intervention.

Data collection will be guided by pretested semi‐structured interview guides developed by the research team based on relevant literature and study objectives. Separate interview guides will be prepared for FGDs, IDIs, and KIIs to ensure context‐specific exploration of issues. The guides will initially be developed in English, translated into Amharic, and back‐translated to ensure linguistic consistency and conceptual equivalence. Necessary revisions will be made following pretesting to improve clarity and contextual relevance.

Face‐to‐face interviews and focus group discussions will be conducted using open‐ended questions supported by probing and follow‐up questions to facilitate deeper exploration of emerging themes. All FGDs, IDIs, and KIIs will be audio‐recorded using electronic devices (smartphones), and field notes will be taken to capture contextual observations and non‐verbal cues. Data collection will take place in private rooms within the outpatient departments (OPDs) or administrative offices of participating hospitals to ensure privacy and minimize interruptions.

The FGDs will be facilitated by experienced moderators fluent in the local language and assisted by trained note‐takers familiar with the cultural context. The principal investigator will supervise all qualitative data collection activities to ensure consistency and data quality. Each IDI and KII is expected to last approximately 40–60 min, while each FGD will last approximately 60–90 min.

Participation in the qualitative study will be voluntary, and written informed consent will be obtained from all participants prior to data collection. Data collection will continue until data saturation is achieved, defined as the point at which no new themes or meaningful insights emerge from additional interviews or discussions.

